#### **Study duration**

It is estimated to take approximately 6 months for each participant. There will be four encounters with the participants (including the baseline) within six months, and each one is expected to last about 30 minutes.

#### **Sampling technique**

A consecutive sampling method will be applied to recruit adult patients who fulfil the inclusion and exclusion criteria upon their visit to the outpatient ENT clinic. When a patient meets the enrolment criteria and agreed for participation, the designated personnel will randomize the subject. Subjects will be randomized using blocked randomization to

randomly assign the participants into control and intervention groups. An excel sheet will be used to generate a block size of 10 random numbers, 5 in each group. Each number will be kept in opaque, sealed envelopes. Consented participants will be instructed to select the sealed envelopes, and the envelopes will be opened by the researchers. The information will be recorded in the screening and enrolment log (appendix C). Subjects will be randomly assigned in a 1:1 ratio to one of two arms: (1) Intervention, or (2) Control. Measure taking to minimise bias

## **Instrument**

### ***Demography and assessment form***

The participants will be asked for their demographic information (date of birth, gender, occupation, ethnicity, and smoking status) and this will be recorded at enrolment. In order to characterise smoking status, the definitions of "current," "former," and "never smoker" were adopted (Centers for Disease Control and Prevention, 2017). Subsequently, participants will be assessed for their medical and allergic history, and information regarding underlying diseases will be recorded at enrolment. This information will be obtained by interview or from patient's medical record by the researcher. Subjective measurement of severity will be graded according to ARIA guidelines at baseline and during follow-ups on day  $60 \pm 7$ ,  $120 \pm 7$  and  $180 \pm 7$ . Objective measurement of disease severity will be determined via endoscopic assessment for middle turbinate oedema grading by the physician at baseline and end of study (Day  $180 \pm 7$ ). The endoscopic assessment is one of the routine tasks that physicians perform to determine the disease progression of AR. The rationale that this assessment be performed at baseline and end of study is based on expert opinions where improvement of the middle turbinate can be seen between 4 and 6 months when patients are adhering to the intranasal corticosteroid treatment. To reduce the burden on the physicians and patients, it is deemed appropriate to schedule patients to come for a clinic visit for this assessment alongside seeking medical consultation.

Their concomitant medications, if any, will be gauged in that all types of medicine that the patient is currently taking or has taken in the last 30 days will be evaluated. This includes all prescribed and over-the-counter medications. The medication dose, route, unit, frequency of administration, indication for administration, and dates of medication will be captured. Concomitant medication of study-specific interest which will be recorded during the study period includes antihistamines, corticosteroids, anticholinergics, leukotriene receptor

antagonists, nasal saline, decongestants, and beta-blockers. This information will be recorded in the demography and assessment form (appendix D).

### ***Measurement knowledge of intranasal corticosteroid***

A self-administered questionnaire evaluating the knowledge of the participants with regards to their understanding of intranasal corticosteroids is adapted. Permission to adapt this questionnaire as well as to perform a translation into Malay language via the process of linguistic validation methodology has been obtained from the originator (copyright holder). The original questionnaire is shown in appendix E (Retinasekharan et al., 2021). The knowledge will be assessed during the baseline data collection, Day 120 $\pm$ 7, and on Day 180 $\pm$ 7.

### ***Measurement of symptoms control***

Total nasal symptom scores (TNSS) (Appendix F), a validated tool that enables patients to self-rate their specific nasal symptoms including nasal obstruction, itching, sneezing, secretion, runny nose, and sleep difficulty on a 4-point Likert scale ranging from 0 (no symptom) to 3 (severe symptom) in the past 12 hours and 2 weeks, is found appropriate to be adapted for symptom control assessment. The psychometric properties of TNSS is belonged to the copyright holder and thus it cannot be shared (Downie et al., 2004). The decision to select this tool is based on careful discussion with the expert opinion (rhinologists) in the consideration of the aspects of its simplicity for administration to the patients, its ability to provide objective measurement of patients' self-reported symptoms, and its potential to be used in daily clinical practice. In addition, TNSS has been widely used in randomised controlled trials and adapted in many countries. It is the most accepted primary efficacy variable that is rated for drug approval in AR by the U.S. Food & Drug Administration (U.S. Food and Drug Administration, 2020). Permission to adapt TNSS to be used in this study has been granted. In addition, permission to translate TNSS into a Malay version has also been granted by following linguistic validation methodology where it involves forward and backward translation, review by clinicians, conduct of cognitive interviews, and proof-reading (Acquadro et al., 2012). Symptom control will be assessed at baseline, on Day 60 $\pm$ 7, Day 120 $\pm$ 7, and Day 180 $\pm$ 7.

### ***Measurement of medication adherence***

A self-developed diary card to record participants' medication adherence levels on their daily use of intranasal corticosteroid and if additional sprays are required (appendix G). The use of diaries that require participants to self-report their adherence is deemed more appropriate as it allows a more precise estimation of the number of days that the participant declares they are taking the medication. The diary card will be pre-tested prior to use. This variable will be assessed on Day 60  $\pm$ 7, Day 120  $\pm$ 7, and Day 180  $\pm$ 7.

### **Measurement of quality of life**

The EuroQoL 5-Dimensions, 5-Levels (EQ-5D-5L) (appendix H), is a validated tool that has fulfilled these considerations. This tool has also been adapted by several allergic rhinitis-related studies and is therefore deemed appropriate to be adapted for this study (Hwang et al., 2019; Kumanomidou et al., 2022). The EQ-5D-5L consists of a descriptive system and the EQ VAS. The descriptive system is comprised of five dimensions (Mobility, Self-Care, Usual Activities, Pain/Discomfort, and Anxiety/Depression), with each dimension consisting of five response levels, namely, no difficulties, slight problems, moderate problems, severe problems, and unable to/extreme problems. Respondents indicate their health by marking the appropriate box for each question. The EQ VAS captures the respondent's total present health on a vertical visual analogue scale labelled "The best health you can imagine" and "The worst health you can imagine." EQ VAS measures a patient's overall health perception (EuroQoL Research Foundation, 2019; Herdman et al., 2011; Shafie et al., 2019) at baseline, on Day 60  $\pm$ 7, Day 120  $\pm$ 7, and Day 180  $\pm$ 7.

### **Study variables**

Table 2 lists the study variables, their descriptions, and the types of variables for the phase-one study.

Table 2: Study variables

| Variables                     | Description                                                                                                                                   | Types of variables |
|-------------------------------|-----------------------------------------------------------------------------------------------------------------------------------------------|--------------------|
| Demography of patients |                                                                                                                                               |                    |
| Age                           | Age of the participants                                                                                                                       | Continuous         |
| Gender                        | The gender of the participants                                                                                                                | Categorical        |
| Highest education level       | The highest education level of the participants                                                                                               | Categorical        |
| Occupation                    | The occupation of the participants will be classified according to the social-economic classification (Office for National Statistics, 2010). | Categorical        |

|                                              |                                                                                                                                                                                                                                                                                                                                                                                                              |             |
|----------------------------------------------|--------------------------------------------------------------------------------------------------------------------------------------------------------------------------------------------------------------------------------------------------------------------------------------------------------------------------------------------------------------------------------------------------------------|-------------|
| Smoking status                               | 
 
Current smoker: <math>\geq 100</math> cigarettes and still smoked daily or quit within 1 year of admission
 
Former smoker is defined as a former smoker smoked <math>\geq 100</math> cigarettes and quit more than 1 year.
 
Never smoke: an adult who has never smoked, or who has smoked less than 100 cigarettes in his or her lifetime.
 
 | Categorical |
| Comorbidity                                  | Comorbidities other than asthma                                                                                                                                                                                                                                                                                                                                                                              | Categorical |
| Asthma                                       | The control of asthma for patients who have concurrent asthma.                                                                                                                                                                                                                                                                                                                                               | Categorical |
| Frequency of AR graded according to ARIA     | Intermittent or persistent AR symptoms                                                                                                                                                                                                                                                                                                                                                                       | Categorical |
| Severity of AR graded according to ARIA      | Mild or moderate/severe AR                                                                                                                                                                                                                                                                                                                                                                                   | Categorical |
| Endoscopy assessment by physician            | Middle turbinate edema grading into normal, focal, multifocal, diffuse, or polypoid edema.                                                                                                                                                                                                                                                                                                                   | Categorical |
| Family history of AR                         | The patient reported an AR family history.                                                                                                                                                                                                                                                                                                                                                                   | Categorical |
| Self-reported triggering allergen (if known) | The patient self-reported known allergen                                                                                                                                                                                                                                                                                                                                                                     | Categorical |
| Concomitant Medication of Interest           | Medication for treating AR                                                                                                                                                                                                                                                                                                                                                                                   | Categorical |
| Knowledge of nasal steroid spray      |                                                                                                                                                                                                                                                                                                                                                                                                              |             |
| Four structured questions                    | The choice of responses is either yes, not sure, or no                                                                                                                                                                                                                                                                                                                                                       | Categorical |
| Total Nasal Symptom Score (TNSS)      |                                                                                                                                                                                                                                                                                                                                                                                                              |             |
| Total Nasal Symptom Score                    | The sum of the scores of the four nasal symptoms self-rated by the patients will be presented as mean and standard deviation                                                                                                                                                                                                                                                                                 | Continuous  |
| Medication adherence                  | The mean adherence rate will be calculated by dividing the number of doses administered with intranasal steroid spray by the total number of doses the intranasal steroid spray is prescribed for. The rate will be presented in mean scores and standard deviation                                                                                                                                          | Continuous  |
| EQ-5D-5L                              |                                                                                                                                                                                                                                                                                                                                                                                                              |             |
| Utility value                                | A utility score will be generated in the form mean and standard deviation                                                                                                                                                                                                                                                                                                                                    | Continuous  |
| Visual analogue scale (VAS)                  | VAS will be generated in the form of mean and standard deviation                                                                                                                                                                                                                                                                                                                                             | Continuous  |

764

765 **Assessment of efficacy**766 **Data collection**

The ENT physicians will screen for potential eligible patients in the ENT clinic and refer them to the researchers. Informed consent must be obtained prior to the participants entering the study and before any protocol-directed procedures are performed. A unique subject identification number (subject ID) will be assigned to each participant; this subject ID will be used throughout the study.

The participants will be asked for their demographic information (date of birth, gender, occupation, ethnicity, and smoking status) and this will be recorded at enrolment. In order to characterise smoking status, the definitions of "current," "former," and "never smoker" were adopted (Centers for Disease Control and Prevention, 2017). Subsequently, participants will be assessed for their medical and allergic history, and information regarding underlying diseases will be recorded at enrolment. This information will be obtained by interview or from medical records. Subjective measurement of allergic rhinitis classification will be graded according to ARIA guidelines at baseline and during follow-ups on day  $60 \pm 7$ ,  $120 \pm 7$  and  $180 \pm 7$ . According to the ARIA guideline, the patients will be asked for their frequency of symptoms experienced, in which intermittent is defined as  $< 4$  days per week or  $< 4$  weeks at a time, while persistent is defined as  $\geq 4$  days per week and  $\geq 4$  weeks at a time. Their severity will be rated either as "mild" as defined as normal sleep, daily activities, work/school and no troublesome symptoms; or "moderate/severe" as defined as one or more of the symptoms, including abnormal sleep, impairment of daily activities, sport, leisure, problems at work or school, and troublesome symptoms. The possible allergic classifications will be intermittent mild, intermittent moderate/severe, persistent mild, or persistent moderate/severe.

Meanwhile, objective measurement of disease severity will be determined via endoscopic assessment for middle turbinate oedema grading by the physician at baseline and on Day  $180 \pm 7$ . The endoscopic assessment is one of the routine tasks that physicians perform to determine the disease progression of AR. The rationale that this assessment be performed at baseline and end of study is based on expert opinions where improvement of the middle turbinate can be seen between 4 and 6 months when patients are adhering to the intranasal corticosteroid treatment. To reduce the burden on the physicians and patients, it is deemed appropriate to schedule patients to come for a clinic visit for this assessment alongside seeking medical consultation.

Their concomitant medications, if any, will be gauged in that all types of medicine that the patient is currently taking or has taken in the last 30 days will be evaluated. This includes all prescribed and over-the-counter medications. The medication dose, route, unit, frequency of administration, indication for administration, and dates of medication will be captured. Concomitant medication of study-specific interest which will be recorded during the study period includes antihistamines, corticosteroids, anticholinergics, leukotriene receptor antagonists, nasal saline, decongestants, and beta-blockers. This information will be recorded in the demography and assessment form (appendix I).

Face-to-face data collection during their physical visit to the ENT clinic will be performed at baseline and end of study follow-up (Day 180 $\pm$ 7). The post randomization follow-ups on 60 $\pm$ 7 and day 120 $\pm$ 7 will be conducted virtually (Zoom, Google Meet, Whatapps call or telephone call) or face-to-face depending on the feasibility and standard operating procedures of the outpatient ENT clinic at Hospital Raja Permaisuri Bainun during the data collection period. The reason for giving an option of virtual follow-up is to avoid adding a burden to the already extensive ENT clinic, which expects a patient load of 80–160 patients with allergic rhinitis every month. However, if the participant's clinic appointment falls on either day 60 $\pm$ 7 or day 120 $\pm$ 7, face-to-face data collection will be performed. A range of plus or minus 7 days is allowed for each scheduled time point. The data that will be collected on 60 $\pm$ 7 and day 120 $\pm$ 7 include disease severity assessment, symptom control assessment, medication adherence, and quality of life.

A checklist is created to ensure that the element of the algorithm of pharmacist management is implemented on participants assigned to the intervention group (Appendix I). Pharmacist-led educational protocol that consists of education material and structured pharmacist counselling. The educational material will be introduced to the participants assigned to the interventional group at baseline while the structured pharmacist counselling will be given to the participant in the interventional group at baseline and on 60 $\pm$ 7, 120 $\pm$ 7 and 180 $\pm$ 7. Table 3 shows a schedule of study procedures.

Table 3: Study schedule

| Timepoint          | Screening,
D0 | Baseline,
D0 | D60 $\pm$ 7 | D120 $\pm$ 7 | D180 $\pm$ 7 |
|--------------------|------------------|-----------------|-------------|--------------|--------------|
| ENROLLMENT: |                  |                 |             |              |              |
| Eligibility screen | x                |                 |             |              |              |

|                                                      |  |   |   |   |   |
|------------------------------------------------------|--|---|---|---|---|
| Informed consent                                     |  | x |   |   |   |
| Randomization                                        |  | x |   |   |   |
| Demography & medical history                         |  | x |   |   |   |
| INTERVENTION:                                 |  |   |   |   |   |
| Educational materials                                |  | x |   |   |   |
| Pharmacist counselling                               |  | x | x | x | x |
| ASSESSMENT:                                   |  |   |   |   |   |
| Disease severity classification using ARIA guideline |  | x | x | x | x |
| Endoscopy assessment                                 |  | x |   |   | x |
| Knowledge level                                      |  | x |   | x | x |
| Symptoms control                                     |  | x | x | x | x |
| Medication adherence*                                |  |   | x | x | x |
| Quality of life                                      |  | x | x | x | x |
| Concomitant medication                               |  | x | x | x | x |

\* Patients will fill-up diary card throughout the study period on medication they have taken

Participants' knowledge levels will be evaluated by self-completing a questionnaire assessing their knowledge (appendix E). Their knowledge level will be evaluated at Day 0 (baseline), Day 120±7, and Day 180±7 during their clinic visit.

Participants' symptom control will be assessed by the researcher using TNSS (appendix F). They will be asked to reflect on their symptoms in the past 12 hours and the past 2 weeks. Symptom control will be monitored at Day 0 (baseline), Day 60 ±7, Day 120±7 and Day 180±7.

Participants' medication adherence levels will be evaluated by asking the subject to record the diary card with details on the prescribed intranasal corticosteroid during the study (appendix G). A nasal spray administration diary card will be given to the participants on Day 0. Their adherence will be assessed during Day 60 ±7, Day 120±7 and Day 180±7. If virtual follow-up is conducted on Day 60±7 and Day 120±7, participants will be asked to take a photo of their diary card and send it to the researchers, while those without a smart phone device will be required to bring along the diary card at the end of follow-up. A phone call will

be made prior to the scheduled visit (Day 180  $\pm$ 7) to remind them to bring along the diary card. If the participants have a scheduled visit at the clinic, they will be asked to bring along the diary card.

The participants' QoL will be evaluated by self-completing EQ-5D-5L (appendix H). Their QoL will be monitored at Day 0 (baseline), Day 60 $\pm$ 7, Day 120 $\pm$ 7 and Day 180 $\pm$ 7. Two sets of paper EQ-5D-5L will be given to participants without a smart phone for them to self-complete at home during virtual follow-up on Day 60 $\pm$ 7 and Day 120 $\pm$ 7, and they are required to bring them along to the clinic (Day 180 $\pm$ 7). Participants with a smart phone will be asked to complete the questionnaire electronically (Google Form) during virtual follow-up on Day 60 $\pm$ 7 and Day 120 $\pm$ 7. If their follow-up appointment is at the same time as a scheduled clinic visit, they can complete the questionnaire on paper or online (using a Google form).

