## Potential Risks

A pharmacist-led educational protocol not only helps patients understand AR management but may also serve as a general guide for healthcare providers to learn about this disease management. This would enable healthcare providers to deliver concordant care in a standardised manner in an effort to achieve medication adherence and attain improved clinical outcomes (Meltzer et al., 2017).

The foreseeable risk to the participants is minimal. The participant who will be assigned at random to either the control or intervention group will be receiving usual care while the intervention group will be receiving a pharmacist-led educational protocol. Physically, there is no investigational product in this study, the participants will not be exposed to any new substances.

The participants will be asked for their demographic details, and they will be asked to self-administer a validated questionnaire assessing their knowledge with regards to intranasal corticosteroid, symptom control, and quality of life. Additionally, they will be given a diary card to record their medication usage. None of the tools used involved any sensitive questions or invasive procedures. The questionnaire administration process and daily recording of medication intake will not affect the participants from psychological, social, legal, or economic perspectives.

The participants will be followed up on day 60 $\pm$ 7, 120 $\pm$ 7 and 180 $\pm$ 7. They will need to allocate some time to answer the questionnaire. The follow-up could be conducted in the form of a physical visit to the clinic should they be scheduled for a doctor's appointment, or they will be followed up virtually using Zoom or Google Meet. No additional expenses will be incurred for the participants. The need for participant follow-up is important to determining the long-term sustainability of knowledge and behaviour change as reflected in the outcomes (symptom control and quality of life) after receiving a pharmacist-led education protocol versus those receiving usual care.

Shortening the duration of follow-up for the participants has been considered. However, in the consideration of the robustness of the pharmacist-led educational protocol, up to 180 days of follow-up would increase the overall effectiveness of the research effort to better convince health policymakers to adapt this protocol for clinical practice (Salkind, 2022).

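### The protocol contradicts itself on who rates TNSS, a primary outcome, and sets no order between assessment and counselling in the intervention arm

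*Combined protocol and SAP*

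**What the plan says.** Section 5 (Study endpoints, Table 1) lists symptom control as a primary endpoint. The documents describe its rating in two ways.

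- **Patient.** The Potential Risks section says of participants that "they will be asked to self-administer a validated questionnaire assessing their knowledge with regards to intranasal corticosteroid, symptom control, and quality of life". The section on measuring symptom control calls TNSS "a validated tool that enables patients to self-rate their specific nasal symptoms". Table 2 defines the score as "The sum of the scores of the four nasal symptoms self-rated by the patients". The form in Appendix F is addressed to the patient.
- **Researcher.** The Data collection text under Assessment of efficacy, which is the operative procedure, says that "symptom control will be assessed by the researcher using TNSS (appendix F").

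The neighbouring outcomes are worded differently: "Participants' knowledge levels will be evaluated by self-completing a questionnaire assessing their knowledge" and "The participants' QoL will be evaluated by self-completing EQ-5D-5L". For EQ-5D-5L the text also sets out how this is done remotely: "Participants with a smart phone will be asked to complete the questionnaire electronically (Google Form) during virtual follow-up", with paper sets for those without a smart phone. TNSS has no such route.

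On timing, the same section says that "structured pharmacist counselling will be given to the participant in the interventional group at baseline and on" Days 60, 120 and 180. Table 3 places consent, randomization, educational materials, counselling and all baseline assessments on Day 0 without a sequence. Under Sampling technique, researchers open the allocation envelopes. The only order stated is in the ethics section: controls receive counselling once, at the end of the study, after their data are collected.

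**The concern.** If the procedure is followed as written, a researcher who may know the allocation takes part in eliciting a 0 to 3 rating of each symptom. In one arm only, this can happen after the patient has been counselled on the same day. Any prompting would then act on one arm and could not be separated from a treatment effect.

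The unstated order also affects outcomes that are plainly self-completed. A knowledge questionnaire filled in after that day's counselling measures what was just heard. The Potential Risks section justifies the long follow-up by the wish to learn whether knowledge is sustained. On Day 0, if the envelope is opened or counselling given first, even the baseline values could be affected in one arm.

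**Working it through.** **1. Who rates.** Three descriptions and the form itself point to the patient; one phrase points to the researcher. Because that phrase sits in the data collection procedure, and knowledge and EQ-5D-5L are called self-completed in the same section, site staff could reasonably act on it.

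**2. Overlap of counselling and assessment (Table 3).**

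| | Day 0 | Day 60 | Day 120 | Day 180 |
|---|---|---|---|---|
| Counselling, intervention arm | yes | yes | yes | yes |
| TNSS | yes | yes | yes | yes |
| EQ-5D-5L | yes | yes | yes | yes |
| Knowledge | yes | no | yes | yes |

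Every TNSS, EQ-5D-5L and knowledge assessment falls on a counselling day, and no before-or-after rule is given for the intervention arm.

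**3. The plan's own TNSS calculation.** Inputs from the Sample size section: means 3.991 and 5.704, SDs 2.2145 (n=181) and 2.2341 (n=182), m=4 measurements, correlation ρ=0.5, alpha 0.05.

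- Pooled SD = √[(180×2.2145² + 181×2.2341²)/361] = 2.2243
- f = (difference/SD)/2 = (1.713/2.2243)/2 = 0.385; the plan uses 0.3850550
- λ = f²·N·m/(1+(m−1)ρ) = 0.3850550² × 36 × 4/2.5 = 8.540
- With 1 and 34 df the critical F is 4.130 and power 0.8103

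This reproduces the stated total of 36; a total of 34 gives 0.786.

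**4. Illustration of what a shift in one arm would do.** The documents give no size for such a shift, so it is an assumption shown over a range. Assume no true effect, N=140 (70 per arm), SD 2.2243, ρ=0.5, and the between-group test of the repeated-measures ANOVA. A shift of b points at the three follow-ups only averages 0.75b over four visits. Then f = 0.75b/(2×2.2243) and λ = f² × 140 × 4/2.5 = 224f².

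| Shift b (TNSS points, scale 0–12) | f | λ | Chance of P<0.05 |
|---|---|---|---|
| 0 | 0 | 0 | 5% |
| 0.1 | 0.0169 | 0.064 | 5.7% |
| 0.25 | 0.0421 | 0.398 | 9.6% |
| 0.5 | 0.0843 | 1.592 | 24.0% |
| 1.0 | 0.1686 | 6.367 | 70.7% |

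If Day 0 were shifted as well, which the open Day 0 order permits, the last column for the four shifts becomes 6.3%, 13.3%, 38.6% and 91.6%. With all 154 participants analysed and only the follow-ups shifted, it is 5.8%, 10.1%, 26.0% and 74.8%. A larger sample does not remove the problem: 140 is already about four times the 36 that the plan needs for TNSS (140/36 = 3.9).

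**The case against.** The strongest reply is that this is a slip of wording. The sentence after the disputed one has participants reflect on their own symptoms over the past 12 hours and 2 weeks, so the researcher may only read the form aloud, which is natural on a telephone or video call. That reading is fair, and it means the documents do not show a decision to have researchers score symptoms. It does not settle the matter: a reader who knows the arm can still prompt, and the descriptions still disagree.

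A reader might also infer more than the text supports:

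- **That the counselling pharmacist collects TNSS.** Pharmacists are listed among the investigators, alongside a medical officer and consultants, but nothing says who collects it.
- **That the TNSS form reveals the arm.** The group tick box is on the Appendix D assessment form, which records ARIA grade, endoscopy, medication and side effects. Appendix F shows no group field. The better evidence that researchers can know the arm is that they open the envelopes.
- **That the trial is stated to be unblinded.** This is inferred from silence. The Sampling technique section ends with a line about minimising bias and no text under it; content may have been lost when the PDF was read, so nothing is built on that gap.
- **That controls have a visit-by-visit order that the intervention arm lacks.** The ethics section describes a single counselling session for controls at the end of the study.
- **That scores will be shifted in favour of the intervention.** This is plausible, but the documents do not show it.

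**Conclusion.** The contradiction over who rates TNSS, and the absence of any order between assessment and counselling in the intervention arm, are both in the text and can be stated with high confidence. That bias follows is a possibility, held with moderate confidence. It depends on the assessor knowing the arm and on an order of events that the documents leave open. The same-day recall concern for knowledge is conditional in the same way.

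Neither size nor direction can be derived from the plan. The illustrative range of about 6% to 71% false-positive results rests on an assumed shift of 0.1 to 1.0 points at the follow-ups, on the plan's borrowed SD and correlation, and on the planned ANOVA. It shows sensitivity and is not an estimate of what will happen. The point is a cheap improvement to the procedure; it gives no reason to change the sample size or the analysis.

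**What to change.** - **Administration.** Amend the TNSS paragraph under Data collection to agree with Potential Risks, the instrument section and Table 2: participants in both arms complete TNSS themselves at every visit, on paper in clinic or by Google Form at virtual visits. Those without a smart phone fill in a paper form at the start of the call and read out the scores. The take-home arrangement for EQ-5D-5L, with paper returned at Day 180, should not simply be copied, because late completion would suit a score with 12-hour recall poorly.
- **Order.** State that in both arms TNSS, EQ-5D-5L and knowledge are completed before the envelope is opened on Day 0 and before any counselling at later visits. Show this sequence in Table 3.

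An alternative for TNSS is one uniform mode of administration by someone who neither knows the arm nor counsels.

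The cost is a small change to forms and visit flow; the visits stay the same. Self-completion removes interviewer influence but not reporting bias, because participants know which arm they are in, and the report should say so. The change belongs before data collection, since scores elicited under the other procedure cannot be corrected afterwards.
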